#### Intervention deliverers

2.3.2.

Two coaches will deliver the interventions of this study. One coach (age at the beginning of the study: 26 years) holds a master's degree in pedagogics, a bachelor's degree in pedagogics with physical education as a minor subject. She has a global trainer's license (i.e., without specialization; “Übungsleitungsschein-C Breitensport”) and comprehensive experiences with instructing children in sport contexts. She will be integral part of the academic team and also contribute conceptually to the design of the study. The other coach (age at the beginning of the study: 25 years) holds a bachelor's degree in health management and has also acquired several coaching licenses (e.g., on fitness and yoga for children), gained comprehensive experiences with instructing children in sport contexts, and will be specifically hired for the practical part of the interventions. The two coaches will also individually supervise and conduct the measurements, while gaining support by a second person (i.e., student assistant or instructed teacher from the local school) for the days of assessment. Blinding of the two deliverers cannot be realized as they were specifically employed for the purpose of this study.

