**Figure 1 F1:**
[figure not shown]
Study design.

After the completion of the two pilot studies, we will follow up with the main study. The main study will more rigorously examine the effectiveness of the final PL intervention in a controlled design. In each school, an even number of classes of one grade level will participate in the study. Half of the classes will be assigned to the intervention condition, which will pass regular half-year education in primary school plus a weekly PL intervention. In contrast, the other half of the classes will be assigned to the control condition, which will undergo only regular half-year education in primary school without the additional PL intervention (see Figure 1). Randomization cannot be fully realized as pragmatic reasons co-influence the assignment to the different intervention arms (57). The main study, which also includes two measurement time points (e.g., pre and post), will take place between September 2023 and February 2024. In summary, the research design with two pilot cycles (51) accounts for potential pitfalls (e.g., revision of PL content) toward a sound examination of the effectiveness of the PL intervention. The final reporting of study will adhere to the recent physical literacy interventions reporting template suggesting a total of 14 items (58). The ethics committee of the University of Oldenburg, Germany, has approved the conduction of the study (sign Drs.EK/2022/057).

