#### Intervention structure, organization, and content

2.3.1.

To develop a holistic, age-specific intervention for 8–11 years old children theoretically based on the PL concept (goal a), we will deliver an intervention program comprising a total of 14 individual sessions. The duration of the sessions will be aligned with the logistic and temporal situation at the recruited schools and can range between 60 and 90 min. To facilitate the arrangement of the school schedules and promote comparability, the frequency of sessions held will be one time per week. Each session will be driven by the concept of PL and will be implemented after the regular classes, e.g., in times of afternoon care, or in some schools in the context of an individual spare time in between the regular school day. In contrast to theory-inspired interventions, theory-based interventions cultivate explicit links between theory and content (70, 71). In the context of this intervention, each session will contain explicit links to all PL domains (see Table 1) in accordance with the selected definition and framework of PL (47): the physical, the cognitive, the affective, and the social domain. All sessions will be realized via actual movement (PA behavior), which implicates that theoretical inputs without an immediate transfer into practice will be avoided across the sessions. In reference to studies which criticized the separation of the different domains in previous PL interventions or the emphasis on a specific domain (the physical domain foremost) (24, 72), our aim will be to consider the integrated nature of PL in every single session. Accordingly, we will not treat the PL domains as isolated blocks, instead addressed the domains in an integrative manner (73).

**Table 1 T1:** A detailed overview of the theory-based PL intervention content.

Session	Main focus	Main goal	Theory-content link			
			Physical domain	Cognitive domain	Psychological (affective) domain	Social domain
1	Evaluation: Pretest	Self-evaluation, enabling PL charting	Mixed rule-based games focusing object control	Content knowledge: Reasons for evaluation	Self-perception	Fairness, inclusion
2	Cooperative game forms	Strengthen group structure	Game arrangements promoting cooperation and anticipation	Strategy and planning; Participatory development and operation with cooperation strategies	Focusing success experiences with the whole group	Communication; respect; solve team challenges

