10	Ball games (Part 2)	Improve object control	Object control (ball); Exercises focusing the reaction time	Knowledge about different types of coordination	Celebrate progress (Ballgames-1)	Playing in different ways together and against each other
11	Trend sport	Learn something new	Object manipulation: throwing and catching a frisbee	Reasoning: issues of being active every day—discuss solutions	Encouragement and motivation to try something new	Trying something new together, society and culture
12	Conditional abilities	Introduction in different conditional abilities, own strengths	Small team games focusing the range of movements running, throwing, pushing	Introduction in knowledge of different abilities to be physical active	Enjoyment of various movements; focusing individual success experiences	Respect individuality; communication, ethics
13	Free session	Enjoyment; implement own movement ideas	Mixed games and exercises	Reflection of “taking home” messages of the program	Involvement; encouragement	Communication; relationships
14	Evaluation: Posttest	Self-evaluation, promoting PL charting	Mixed rule-based games focusing object control	Changes in PA/sport habits before and after	Self-perception	Respect towards others, fairness

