The intervention will be designed as a 14 week-program, while evaluations (pre and post) will be integrated into the first and last session. In addition to the scientific purpose, the evaluation will promote individuals' charting of PL, thus enabling reflections about one's journey and progress (74). Irrespective of these evaluation sessions, each session will contain a specific topic. In line with Whitehead (75) who emphasized the benefit of offering a wide range of contents to enhance the motivation of children to become physically active, we will cover a broad range of physical activities across the entire program, as PL (with its holistic and monistic view) advocates for engaging in encompassing physical activities and for making experiences with their own physical capacities (22, 60). We will consider rule-based games, aesthetic movements, movements with and on equipment, racket sports, scuffling, and basic forms of fitness (76). More specifically, we will realize rule-based games primarily via ball games and racket sports; the aesthetic input will focus on dancing and acrobatics, and fitness will be dominantly targeted via endurance-oriented games or in the context of parkour (for details, see Table 1). Furthermore, differentiations (taxonomies) between locomotion vs. object control (77) as well as individual vs. team activities (78) will guide the intervention to cover the breadth of movement forms and experiences. We will concentrate on land-based experiences, as aquatic activities cannot be realized for logistic-pragmatic and legal-qualificatory reasons.

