#### Behavioral domain

2.5.5.

In the pilot study, the participating children will be invited to indicate leisure-time sports and the number of days within a week with a daily PA level above the WHO recommendation of 60 min. The number of days corresponds to the CAPL-2 survey (85).

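### Unblinded coaches measure the outcomes inside the programme's first and last sessions, so measurement conditions at post-test differ by arm and can bias the time-by-group interaction

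*Protocol article*

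**What the plan says.** Section 2.3.2 gives outcome assessment to the deliverers: "The two coaches will also individually supervise and conduct the measurements, while gaining support by a second person". The second person is a student assistant or an instructed teacher from the school. On blinding, the same section says: "Blinding of the two deliverers cannot be realized as they were specifically employed for the purpose of this study".

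Section 2.3.1 places the measurements within the programme: "evaluations (pre and post) will be integrated into the first and last session". It gives them a second role: "In addition to the scientific purpose, the evaluation will promote individuals' charting of PL, thus enabling reflections about one's journey and progress". Table 1 lists content in all four domains for both evaluation sessions. The cognitive entry is "Content knowledge: Reasons for evaluation" in session 1 and "Changes in PA/sport habits before and after" in session 14.

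Section 2.1 describes the control classes as a group "which will undergo only regular half-year education in primary school without the additional PL intervention".

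Section 2.7.2 makes the time-by-group interaction of a repeated MANOVA the main test, with class entered as a covariate. The limitations in 3.2 cover aquatic activities and the lack of randomisation. They mention neither unblinded assessment nor unequal measurement conditions.

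**The concern.** The reason given for not blinding applies to delivery. It does not explain why the deliverers must also measure. One of the two coaches also belongs to the academic team and conceptualises the session content (2.3.2, 2.3.3), so a designer of the programme helps to measure whether it works.

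The more specific problem is that the measurement is itself part of the programme in one arm only. By session 14, intervention children have had twelve content sessions (2 to 13) with a coach, and they are assessed in a session designed to make them look back on their progress. Control children have neither experience. A child may rate themselves more favourably, or try harder on a motor test, for someone they know and in that context. An unblinded tester may also encourage or score differently. Any such effect would appear as better development in the intervention arm, which is the study's main hypothesis (1.3). The abstract says the results will decide on scale-up.

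**Working it through.** **1. Which part does not cancel.** Write the observed difference in change as

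D = true effect + (m_I,post − m_I,pre) − (m_C,post − m_C,pre),

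where m is the influence of the measurement conditions in the intervention (I) or control (C) arm. An influence that is the same at both times within an arm drops out. This would include the mere fact of being tested in a programme session, if its effect were constant. What remains is whatever changes between sessions 1 and 14:

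| Feature | Intervention, pre | Intervention, post | Control, pre and post |
|---|---|---|---|
| Place of measurement (2.3.1; 2.1) | programme session 1 | programme session 14 | not in a programme session |
| Cognitive content listed (Table 1) | reasons for evaluation | changes in activity habits | none |
| Content sessions already held (Table 1) | 0 | 12 | 0 |

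Familiarity with the coach and reflection on progress can differ from the control arm only at post-test. They therefore fall on the interaction. They coincide with arm, so entering class as a covariate cannot separate them from the treatment effect.

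**2. The plan's own figure.** Inputs from 2.6: f = 0.15, alpha = 0.05/5 = 0.01, r = 0.50, power at least 80%. There are two time points (m = 2).

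- Noncentrality λ = f²·N·m/(1 − r) = 0.0225 × 134 × 2/0.5 = 12.06.
- An F test with 1 and 132 degrees of freedom then has power 0.803, so N = 134 reproduces.
- 134/0.75 = 179 children, or 8.95 classes of 20.
- A one-sided test at 0.01 would need 116, so the stated 134 corresponds to the ordinary F test.

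**3. What a given bias would do.** The documents give no bias size, so b below is an assumption. Suppose there is no true effect and unequal measurement shifts the difference in change by b, in units of the single-occasion SD. With r = 0.5 the SD of change is √(2(1 − 0.5)) = 1 such unit, so the noncentrality of the t statistic is b·√134/2 = 5.79·b. Clustering is ignored.

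| b (assumed) | Noncentrality | Favourable significant result, two-sided 0.01 | One-sided 0.01 |
|---|---|---|---|
| 0 | 0 | 0.005 | 0.010 |
| 0.05 | 0.289 | 0.011 | 0.021 |
| 0.10 | 0.579 | 0.023 | 0.040 |
| 0.20 | 1.158 | 0.076 | 0.119 |
| 0.30 | 1.736 | 0.195 | 0.272 |

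For fixed b the noncentrality grows with √N, so a larger sample makes a false positive more likely. The scale of b should not be read against the plan's d = 0.30. The planned λ of 12.06 corresponds to a difference in change of √12.06 × 2/√134 = 0.60 on this scale.

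**4. The activity item.** Section 2.5.5 counts "the number of days within a week with a daily PA level above the WHO recommendation of 60 min" and does not say which week. If it were the past week, session 13 could add a qualifying day in the intervention arm at post-test only. Let p be the chance that the day would have counted anyway, and q the chance that the session makes an otherwise non-qualifying day count. The shift is q(1 − p)/SD. All values here are assumed:

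- q = 1: p = 0.7, SD 2.5 gives 0.12; p = 0.5, SD 2 gives 0.25; p = 0.3, SD 1.5 gives 0.47.
- q = 0.5: 0.06 to 0.23 over the same range.
- q = 0: 0.

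So the shift would lie between 0 and about 0.47 SD, for one of five outcomes.

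**The case against.** The strongest reply is that the article does not describe how control classes are measured. A condensed article may leave assessment logistics to the full protocol, and that silence is not an error. This is right as far as it goes. But the article itself fixes who measures and where in the intervention arm, and it states that controls receive no programme sessions. The difference in setting, content and familiarity follows from those statements.

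Several stronger readings are tempting but not supported:

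- **That the same coaches test the control classes, or that each coach tests the classes they taught.** The first is a natural reading of 2.3.2 but is not stated. The second is not stated either.
- **That children answer after discussing their changed habits.** The order within session 14 is not given. Reflection may follow the measurement.
- **That nearly all outcomes are self-report.** The social and behavioural domains are. The physical domain adds eight DMT tests, described as objective. The cognitive and affective instruments are still to be selected, and one cognitive candidate is CAPL-2 knowledge questions (2.5, 2.5.2).
- **That the treatment is counted as its own outcome.** This needs a past-week item, which 2.5.5 does not specify. A usual-week item would largely remove it. Sessions may last only 60 minutes and include theory inputs and breaks, so a session need not produce a qualifying day. Whether programme activity is an artefact or part of the effect also depends on what the study wants to estimate.

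The article also openly says that the deliverers are unblinded. That disclosure does not extend to their role as assessors in the limitations section.

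**Conclusion.** The concern holds in a limited form. Unblinded deliverers conduct the measurements, those measurements sit inside programme sessions that serve reflection on progress, and the control arm has no such sessions. Measurement conditions at post-test therefore differ by arm, and the difference falls on the primary interaction.

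The direction is most plausibly towards the intervention for self-reported domains. This is a judgement, as the documents give neither direction nor size. The DMT is less open to it but is also run by the coaches. The false-positive figures above are illustrations that rest on an assumed shift, no true effect and no clustering. The counted-session argument is conditional on past-week recall, has a floor of 0, and does not justify rewording an item meant to match CAPL-2.

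The stated sample size is not in question. The bias should be reduced in the design, because it cannot be removed in the analysis.

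**What to change.** For the main study:

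1. Let the second person already planned for assessment days, preferably a student assistant who is not told the class's condition, administer the questionnaires and score the DMT in both arms from one common script. The coaches only organise. Where this is not possible, no coach should measure a class they taught.
2. In the intervention arm, complete all measurements before any programme content or reflection in sessions 1 and 14. Use the same procedure and time window as in the control classes, and say so.
3. Add unblinded assessment, and any remaining difference in measurement conditions, to the limitations in 3.2.

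The cost is mainly reassigning tasks among staff already planned, training assistants in DMT scoring, and small timetable changes. Blinding may be only partial, since an assistant entering a programme session may recognise the condition. Separating delivery from assessment and using one script would still reduce the bias.

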#### Specific training of deliverers

2.3.3.

Both coaches will be trained with key elements of the theoretical interpretation of the construct PL prior to the start of implementation. In this context, the coaches will familiarize themselves with the translation of PL in a teaching and learning process (59, 75). The first coach will take a decisive mediator role for the entire training process by (a) being part of the academic team and its scientific discussions of PL, (b) conceptualizing the intervention content and its translation into PL session documents (manual based), and (c) organizing conceptual exchange about PL in general and the 14 sessions in specific. To foster the conceptual rigor in the scope of the implementation, both coaches will undergo external training during the pilot phase by completing a PL development workshop offered by the International Physical Literacy Association (IPLA).

### Qualitative instruments

2.4.

Following the intention to advance the initial intervention program toward the examination of intervention effectiveness in the main study and to gain subjective perspectives of intervention participants, we will integrate a comprehensive qualitative approach within the pilot studies (cycles 1 and 2). In this context, we will focus on the perspective of the intervention deliverers, on the one hand, and the subjective perspective of the participating children, on the other. Moreover, we will install a multiperspective panel to cultivate regular discussions on the delivery and to enable instant revisions of intervention sessions during the intervention phases (formative evaluation). Depending on the results of the qualitative evaluation within the pilot studies, we strive to maintain the qualitative interviews with the children for the main study as well, as they might give relevant insights and experiences beyond the quantitative approach. All interviewees will have to provide informed consent to participation. All children additionally have to return written consent by their legal guardian.

#### Perspective of intervention deliverers: intervention documentation

2.4.1.

To cover the perspective of the intervention deliverers, we will use intervention documentations for each group at the schools and for each session by recording basic information (e.g., start and end time of the intervention, number of participants, name of the school, topic of the session) as well as general feedback toward the session (practicability of games, exercises, the basic structure of the session), potential adaptions and necessary modifications, other incidents (e.g., delays, disputes of children with the coach, issues with the setting) and, finally, the confidence of the deliverer throughout the single session.

#### Multiperspective panel for intervention discussion and revision

2.4.2.

Moreover, the delivery of the interventions will be accompanied by meetings of an installed panel. This panel can be characterized as: *multiperspective* (as it combines the perspectives of the coaches, of the scientific team, and of the youth welfare service), *multiprofessional* (as it brings together persons from different professional backgrounds and traditions (i.e., general pedagogy, psychology, sport science, health management, social pedagogy) (81), and *transdisciplinary* (as it enables cooperation between researchers and practitioners) (56). These meetings will be held weekly and should, on average, comprise 4–5 participants per session. More specifically, this panel will start with reports of the coaches sharing their concrete experiences from the previous delivery and will lead into open discussion afterwards (see Figure 2). On the one hand, the panel will debate general pedagogical issues (such as the management of children who regularly disrupt the delivery and atmosphere), feedback given by relevant actors of a setting, and restrictions in the intervention settings (e.g., problems in equipment, schedules, room capacities, or in communication with schools and teachers). On the other hand, the panel will also address difficulties with the translation of the PL concept into practice (e.g., challenges with the holistic claim of PL and the associated complexity in delivery). In any case, the defined moderator (rotational procedure) will attempt to maintain a constructive and solution-orientated atmosphere within the session.

**Figure 2 F2:**
[figure not shown]
The role of the multiperspective discussion panel for the revision of the intervention (icons were taken from www.flaticon.com).

#### Perspective of the participating children: group interviews

2.4.3.

As the third part of the qualitative approach, we will interview children after the pilot cycles 1 and 2 (depending on the results, potentially also after the main study) to gain insights into the perspective of participants. More specifically, we will ask the children about their favourite and less favourite topics throughout the interventions (inclusing the underlying reasons), their individual learning achievements, suggestions for the intervention deliverers to improve, and finally their perspective on further participation. We plan to perform 3–5 group interviews, each with 3–6 participating children. Group interviews are defined as semi-structured interviews, focused on a specific topic or theme and guided through the interviewer (54). In this context, we will consider important principles for taking interviews with children, such as a sufficient familiarization with the setting, provision of privacy, the maximum length of the interview, and a trustworthy atmosphere between the interviewer and the participating children (55). Moreover, with a focus on our target group and their level of communicative skills we designed the interview with child-specific incentives and an age-appropriate language (82). The arrangement of a group situation within the interview contributes to overcome potential barriers such as generation differences or dominance relations and is further similar to common school arrangements (82, 83). The group interviews will be led by the second author (LS) and will take place after the quantitative evaluation within selected, interested schools.

